Complications due to the puncture are assessed by post-procedure scanning with an ultrasound device and observation in the surgical field. Complications due to drug administration are assessed based on changes in vital signs. The content, extent, treatment, outcome, and severity of the complications are recorded in the medical record and case report, and follow-up surveys are conducted if necessary (those due to the administration of general anesthesia are not covered). If an adverse event occurs, medically necessary treatment and care will be provided under the guidelines of national health insurance, even after the completion of the trial.

Participant timeline

The timeline of participants is shown in the table below (Table 4).

**Table 4 TAB4:** The participant timeline. X indicates timing of enrolment, intervention, and assessments. - indicates not applicable.

	Screening Period	Study Period				
Time point	From surgery decision to the day before surgery	On the day of surgery				The day after surgery
		Anesthesia induction	Skin incision	Median sternotomy	End of surgery	
Obtaining consent	X	-	-	-	-	-
Eligibility screen	X	-	-	-	-	-
Registration	X	-	-	-	-	-
Check vital signs	X	X	X	X	X	X
Ultrasound pre-scan of the puncture site	-	X	-	-	-	-
Intervention (transversus thoracic muscle plane block)	-	X	-	-	-	-
Ultrasound post-scan of the puncture site	-	X	-	-	-	-
Check for muscle relaxation	-	X	-	-	-	-
Primary outcome	-	-	X	-	-	-
Secondary outcome	-	-	-	X	-	-
Check for postoperative surgical site infection	-	-	-	-	-	X
Check for postoperative pneumonia	-	-	-	-	-	X
Safety assessment	X	X	X	X	X	X

Sample size

A stopping rule is necessary in dose-finding studies based on a BC-UDM [15]. A minimum sample size of n = 50-60 is recommended for calculating EC90 [14]. The stopping rule is set at 45 successful blocks [16]. The target sample size is thus 70 cases, with an estimated dropout rate of 10%.

Recruitment

Prior to the day of surgery, researchers will review the medical records of patients scheduled for surgery and determine potential participants based on the inclusion and exclusion criteria. Researchers will then visit the patients and ask them to participate in the study.

Assignment of interventions: allocation

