In the first case, 0.2% ropivacaine is used. In subsequent cases, the concentration of ropivacaine is to be determined based on the success or failure of the previous block according to a BC-UDM (Figure 1) [14-16]. For the calculation of EC90, if the previous block was unsuccessful, the next higher concentration (increased or decreased by 0.025%) is to be used, and if the block was successful, there is an 8/9 chance of using the same concentration and a 1/9 chance of using the next lower concentration. The floor dose of ropivacaine is 0.1% and the ceiling dose is 0.4%. If the floor dose of 0.1% ropivacaine is successful, the next patient will be assigned to the same concentration (0.1%) and, if the ceiling dose of 0.4% ropivacaine is unsuccessful, the next patient will be assigned to the same concentration (0.4%). Randomization of successful blocks is to be performed using computer-generated random numbers. The patients are to be registered after obtaining consent. The biostatistician of the study will create the random allocation sequence and communicate it by email to the researcher (YN) in charge of allocation. YN will then enroll and allocate participants.

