**Figure 1 FIG1:**
[figure not shown]
Flow chart of allocation procedure.

Blinding

The researcher who will not perform TTPB is informed of the allocation and will have the local anesthetic prepared outside the operating room before the patient enters the room. The concentration of the local anesthetic is not to be written on the syringe so that study participants and the researcher who will perform TTPB (KT) will be blinded to the ropivacaine concentration.

The researcher performing the TTPB and blinded to the concentration of ropivacaine (KT) will assess whether the TTPB is successful or not, and will collect data at the start of surgery. Another member of the research group who is not blinded to the concentration of ropivacaine (MO) will collect the remaining perioperative data.

Data collection

Research data for this study will be collected from electronic medical record systems or case report forms (CRFs). Preoperative data, including demographics, medical history, medication history, laboratory test results, and preoperative evaluations, will be completed on a CRF by the investigator prior to surgery.

Data management

All data will be anonymized and CRFs and electronic data will be coded with a subject identification code. Electronic data recording media and paper documents will be stored on lockable shelves in a lockable room and kept locked at all times. Deleted information, etc., will be stored in a file/folder separate from the analysis data with a password and managed by the principal researcher. As this is personal information, it will be recorded as an electronic file using a computer that is not connected to the Internet and will be password-locked on recording media outside the computer.

Statistical methods

Primary Outcome

The EC90 is defined as the dose of ropivacaine at which successful block was observed in 90% of patients in the study population. EC90 will be calculated using isotonic regression [14-16]. The estimator to be used for isotonic regression is the adjusted success rate of block at each concentration, estimated by the pooled-adjacent-violators algorithm (PAVA) [15,16]. The 90% confidence interval for the isotonic regression estimate of EC90 (Û3) is to be calculated using the bias-corrected percentile method using 2000 bootstrap replicates of Û3 [15,16]. All statistical analyses will be conducted with R version 4.5.0 or later (R Core Team, Vienna, Austria).

Secondary Outcomes

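### The target of 70 does not follow from the 45-success stopping rule and 10% dropout, and that rule does not secure the minimum of 50-60 that the protocol cites

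*Protocol article*

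**What the plan says.** The Sample size paragraph of the protocol article (Materials and methods) makes three statements in succession:

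- "A minimum sample size of n = 50-60 is recommended for calculating EC90", attributed to one cited source.
- "The stopping rule is set at 45 successful blocks", attributed to another.
- "The target sample size is thus 70 cases, with an estimated dropout rate of 10" per cent.

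The third is worded as a consequence of the other two. The paragraph gives no expected number of evaluable patients under the stopping rule. It does not say whether 70 is a maximum, or whether recruitment goes on to 50 or 60 evaluable patients if 45 successes come sooner.

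The section on allocation fixes the scheme that determines how fast successes accrue. "In the first case, 0.2% ropivacaine is used"; the step is 0.025%; a failure moves the next patient up one step; a success keeps the concentration with chance 8/9 and lowers it with chance 1/9; the floor is 0.1% and the ceiling 0.4%.

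**The concern.** A reader takes 70, less 10% dropout, as the size of the study. The rule that actually ends recruitment counts successes only, and at the success rate the design aims for it is met well before 63 evaluable patients. So the stated size and the size the design delivers are different quantities, and the link claimed between them does not hold.

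The stopping rule also sits unreconciled beside the cited minimum. Since the rule is blind to the total number of patients, it can end the trial below 50, and it does so most often when the starting concentration already works well. EC90 is the sole primary outcome, and the number of evaluable patients is the only safeguard on its precision that the paragraph offers. It should be clear what number is promised.

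**Working it through.** **Inputs from the protocol.** Minimum 50-60; stop at 45 successes; 10% dropout; target 70; target success rate 0.90; start 0.2%, step 0.025%, coin 1/9 down after a success, floor 0.1%, ceiling 0.4% (13 levels).

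**Step 1: try to reproduce 70.** Registered = evaluable / (1 − 0.10); the cruder evaluable × 1.10 is shown where it differs after rounding up.

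- 45 → 45/0.9 = 50
- 50 → 50/0.9 = 55.6, so 56
- 55 → 55/0.9 = 61.1, so 62 (or 61)
- 60 → 60/0.9 = 66.7, so 67 (or 66)
- Backwards: 70 × 0.9 = 63 evaluable

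Only 63 evaluable returns 70, and 63 appears nowhere in the protocol.

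**Step 2: what the stopping rule needs at a constant success rate.** With success probability p, the number of evaluable patients is N = 45 + failures, where failures are negative binomial and E(N) = 45/p.

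- p = 0.95: mean 47.4, 95% range 45-51, P(N<50) = 0.90
- p = 0.90: mean 50.0, 95% range 46-55, P(N<50) = 0.45, P(N>63) below 0.0001
- p = 0.85: mean 52.9, 95% range 48-60, P(N<50) = 0.12
- p = 0.80: mean 56.3, 95% range 50-64, P(N<50) = 0.02

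At the target rate the rule therefore implies 50 evaluable and 50/0.9 = 56 registered.

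**Step 3: the protocol's own allocation scheme.** The success rate is not constant, because concentrations move. The true EC90 and the slope are not given, so they are assumed: logistic curves with EC50/EC90 of 0.5 and of 0.7, and a range of EC90 values. Each setting was simulated 20,000 times, stopping at 45 successes. Ranges span the two curves.

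| True EC90 (%) | Mean N | 95% range | P(N<50) | P(N≥60) | P(N>63) |
|---|---|---|---|---|---|
| 0.10 | 46 | 45-49 | 0.99 | 0 | 0 |
| 0.125 | 47 | 45-51 | 0.90-0.92 | 0 | 0 |
| 0.15 | 48 | 45-52 | 0.74-0.76 | 0 | 0 |
| 0.20 | 50 | 47-54 | 0.35 | 0 | 0 |
| 0.25 | 52 | 49-56 | 0.05-0.07 | ≤0.001 | 0 |
| 0.30 | 54 | 50-58 | <0.01 | <0.01 | <0.001 |
| 0.35 | 56 | 52-60 | 0 | 0.03-0.05 | <0.001 |
| 0.40 | 58-59 | 54-64 | 0 | 0.19-0.38 | 0.01-0.03 |
| 0.45 | 60-65 | 55-72 | 0 | 0.55-0.93 | 0.11-0.59 |
| 0.50 | 63-74 | 57-86 | 0 | 0.87-1.00 | 0.45-0.99 |

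P(N<50) at an EC90 of 0.20% is lower than the 0.45 of Step 2 because the scheme corrects itself: successes tend to lower the concentration and so bring failures.

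The slope matters little up to 0.35%. At 0.40%, curves steeper than the two tabulated raise the mean to about 62 and the upper end of the 95% range to about 68.

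**Step 4: size of the shortfall.** N cannot be below 45, so the gap to 50 is at most 5 patients. Among trials stopping below 50, the mean gap is about 1.6 at an EC90 of 0.20% and about 3 at 0.125%. Adding a floor of 50 evaluable patients changes the root-mean-square error of the isotonic EC90 estimate as follows (EC50/EC90 = 0.5; 0.7):

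- EC90 0.125%: 0.0258 to 0.0243; 0.0197 to 0.0181
- EC90 0.15%: 0.0242 to 0.0237; 0.0171 to 0.0164
- EC90 0.20%: unchanged (0.0245; 0.0172), and essentially unchanged above that

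The largest gain, 0.0197 − 0.0181 = 0.0016 percentage points of concentration, is small beside the 0.025 step.

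**The case against.** The best defence is that 70 is the upper recommended minimum allowing for dropout, 60/0.9 = 67, rounded up. In a sequential design the final number is random, so a figure above the expected need is a sensible recruitment allowance. That is plausible and, if meant, conservative. But the text calls 70 a target and presents it as derived, and it states neither the rounding nor the allowance. A fuller protocol may contain the derivation; the published paragraph still asserts a step that its own figures do not support.

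Second, 45 successes and 50 patients agree in expectation, since 45/0.9 = 50, and the cited source may mean 50-60 as a planning size. This stands as far as it goes: the protocol does not promise 50 evaluable patients in every realisation, and the sources cannot be consulted here. It is a reason to state which is meant.

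Third, a reader might infer that stopping below 50 materially harms the EC90 estimate. Step 4 does not support that.

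Fourth, a reader might infer that 70 is simply too many and that recruitment should be capped hard at 63 evaluable. The documents do not support that either. The protocol calls EC90 undetermined and provides for failures at the ceiling. If EC90 is 0.45-0.50%, more than 63 evaluable patients are needed with probability 0.11-0.99, so such a cap could end the trial before 45 successes.

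**Conclusion.** The point holds as a fault of derivation and internal consistency, and should be corrected. That 70 does not follow from the stated inputs is plain arithmetic and needs no assumption. That the rule does not secure 50 evaluable patients follows from the rule itself; how often it falls short depends on an EC90 and slope that the protocol does not give.

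The mean of about 46-59 is a range across assumed scenarios, not a prediction of where a given trial ends. Individual trials run from about 45 to 64 for an EC90 of 0.10-0.40% under the two main curves, and further with steeper curves at the ceiling. The high probabilities of stopping below 50 apply when EC90 is below the 0.2% start; from 0.30% upwards the problem practically vanishes. The consequence is a misstated size and an unclear rule. It is not a material loss of precision, and it does not show that 70 is an unsuitable maximum.

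**What to change.** In the Sample size paragraph:

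1. State that 45 successes are expected to need about 50 evaluable patients (about 56 registered) at the target rate. Add that means of about 46-59 evaluable are expected for a true EC90 of 0.10-0.40%, with individual trials at about 45-64, and give the assumed curves.
2. Describe 70 registered (about 63 evaluable at 10% dropout) as a recruitment maximum and not as a derived target. State which governs if 70 is reached before 45 successes.
3. Reconcile the rule with the cited minimum in one of two ways: require at least 50 evaluable patients as well as 45 successes, or state that 50-60 is an expected size and not a floor.

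Items 1 and 2 cost wording, plus one decision that the trial would otherwise have to make ad hoc. In item 3, the second option is wording only. The first is a small design change: it adds at most 50 − 45 = 5 patients, within the 70, for a small gain in precision, and should be adopted before the 45th success. No hard cap at 63 evaluable is needed.

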**Figure 1 FIG1:**
[figure not shown]
Flow chart of allocation procedure.

Blinding

The researcher who will not perform TTPB is informed of the allocation and will have the local anesthetic prepared outside the operating room before the patient enters the room. The concentration of the local anesthetic is not to be written on the syringe so that study participants and the researcher who will perform TTPB (KT) will be blinded to the ropivacaine concentration.

The researcher performing the TTPB and blinded to the concentration of ropivacaine (KT) will assess whether the TTPB is successful or not, and will collect data at the start of surgery. Another member of the research group who is not blinded to the concentration of ropivacaine (MO) will collect the remaining perioperative data.

Data collection

Research data for this study will be collected from electronic medical record systems or case report forms (CRFs). Preoperative data, including demographics, medical history, medication history, laboratory test results, and preoperative evaluations, will be completed on a CRF by the investigator prior to surgery.

Data management

All data will be anonymized and CRFs and electronic data will be coded with a subject identification code. Electronic data recording media and paper documents will be stored on lockable shelves in a lockable room and kept locked at all times. Deleted information, etc., will be stored in a file/folder separate from the analysis data with a password and managed by the principal researcher. As this is personal information, it will be recorded as an electronic file using a computer that is not connected to the Internet and will be password-locked on recording media outside the computer.

Statistical methods

Primary Outcome

The EC90 is defined as the dose of ropivacaine at which successful block was observed in 90% of patients in the study population. EC90 will be calculated using isotonic regression [14-16]. The estimator to be used for isotonic regression is the adjusted success rate of block at each concentration, estimated by the pooled-adjacent-violators algorithm (PAVA) [15,16]. The 90% confidence interval for the isotonic regression estimate of EC90 (Û3) is to be calculated using the bias-corrected percentile method using 2000 bootstrap replicates of Û3 [15,16]. All statistical analyses will be conducted with R version 4.5.0 or later (R Core Team, Vienna, Austria).

Secondary Outcomes

Summary statistics will be calculated. Exploratory model analyses may be performed as needed.

## Results

Dissemination plans

This is an ongoing study protocol and the results are going to be collected and analysed in 2027. The results of this study will be presented at relevant scientific conferences and published in peer-reviewed journals. The datasets used and analysed during the current study are available from the Principal Investigator on reasonable request. Although patients and members of the public were not directly involved in the design or conduct of the trial, the Institutional Review Board reviewing this protocol includes patient and public representatives. These members contribute to the ethical oversight of the study by providing perspectives on participant burden, informed consent materials, and the relevance of study outcomes to the patient community.

## Discussion

This study was designed to investigate the effect of TTPB on wound pain at the start of surgery. To our knowledge, no studies have investigated the direct effect of fascial plane block on wound pain at the start of abdominal or thoracic surgery in adults. Therefore, the methodology of this study can be considered novel.

Ultrasound-guided fascial plane blocks are a method of injecting a local anesthetic between two fascial layers to block the nerves that innervate the intermuscular layers, providing analgesia over a relatively large area, such as the chest or abdominal walls. This type of regional anesthesia is relatively easy to perform and has a low risk of complications [24, 25]. Ultrasound-guided TTPB, a type of fascial plane block, is effective for treating wound pain following median sternotomy because it is localized at the fascial plane between the transverse thoracic muscle and the internal intercostal muscles to provide analgesia in the anterior cutaneous branch area of ​​the intercostal nerves (T2-6) in the anterior chest [9, 10]. Unlike paravertebral and erector spinae plane blocks, this technique retains the advantages of compatibility with the supine position and does not require positioning in high-risk patients. On the other hand, it has been reported that chest wall nerve blocks result in faster absorption of local anesthetics and are more likely to increase blood concentrations of local anesthetics than nerve blocks in other body areas [26]. As there is limited literature on the application of ultrasound-guided TTPB in cardiac surgery, reporting the appropriate dose of ropivacaine used for ultrasound-guided TTPB will contribute to patient safety by reducing the risk of local anesthetic toxicity while obtaining adequate analgesia.

Enhanced Recovery After Surgery (ERAS) guidelines for cardiac surgery have highlighted perioperative pain, prolonged mechanical ventilation, and bed rest as important factors for patients remaining hospitalized after cardiac surgery [27, 28]. Although new cardiac surgery approaches, such as minimally invasive cardiac surgery and robotic-assisted surgery, have emerged, median sternotomy is still used in cardiac surgery, but is known to be extremely painful [1,2]. Opioid-based “balanced anesthesia” has long been used in cardiac surgery to achieve good perioperative analgesia in cardiac surgery [2, 28]. However, considering side effects (e.g., nausea, vomiting, sedation, and/or respiratory depression) [3], opioid-based analgesia management for cardiac surgery needs to be reconsidered. Recently, multimodal pain management, including regional anesthesia, has become an important component of ERAS [2, 29]. The use of ultrasound-guided TTPB in combination with median sternotomy wound analgesia may help reduce opioid use [10-12] and opioid-related side effects, shorten ICU and hospital stays, contribute to the refinement of multimodal analgesia and ERAS protocols, improve the quality of postoperative rehabilitation, and promote the optimization of healthcare resource utilization. To clarify the EC90 of ropivacaine for TTPB will contribute to patient safety by reducing the risk of local anesthetic toxicity while obtaining adequate analgesia. The finding of an adequate ropivacaine dose will provide a benchmark for setting ropivacaine doses in future, randomized, controlled trials on TTPB.

This study has several limitations. First, because this study will be conducted at a single institution, it is possible that the patient background, anesthesia management, and surgical procedures may contain factors unique to our institution. Therefore, the external validity of the results of this study is limited, and generalization to other institutions or different patient populations requires careful interpretation. Second, this protocol was primarily aimed at investigating the effectiveness of TTPB on surgical site pain at the start of surgery. Thus, further randomized, controlled trials are needed regarding postoperative recovery, postoperative acute pain, and chronic pain. In addition, in this study, TTPB is to be performed before surgery, but the optimal timing for TTPB remains unknown. Based on the results of this study, future prospective, comparative studies are needed regarding the timing of TTPB, either before or after surgery, or both before and after surgery. Even taking these limitations into account, this study is considered significant given its contribution to improving perioperative analgesia, reducing opioid consumption, and avoiding local anesthetic toxicity. In addition, there have been no previous reports examining the effective concentration of local anesthetics used for ultrasound-guided nerve blocks at the start of cardiac surgery, and this study proposes a new approach.

## Conclusions

In summary, this study is to be a dose-finding study using a biased coin up-and-down method. To our knowledge, this is the first study aimed at determining the EC90 of TTPB under ultrasound guidance that will contribute to the growing body of evidence on TTPB. More broadly, this study will help promote multimodal pain management to spare opioid use in cardiac surgery.
